**Recruitment {15}**

As a first step, all the physicians that prescribed nimodipine during the last quarter of 2018 were selected. As a second step, we removed outlier prescribers. Based on previous literature (Hallsworth et al., 2015), the outlier threshold was set at the 97,5th percentile of nimodipine box prescriptions over the last trimester of 2018. As a third step, once outliers were removed, the top 25% prescribers of nimodipine were selected. From this sample, all the participants that remain as providers at the INSSJP-PAMI before the intervention begins and whose e-mail address is active will be randomized to control or treatment arm.

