## **Objectives {7}**

The main aim of this study will be to test the effectiveness of a social norm feedback intervention to reduce the unnecessary prescription of nimodipine by general practitioners within the National Institute of Social Service for Retired and Pensioners (INSSJP-PAMI) in Argentina. As secondary objectives, we will address four additional issues. First, we will assess the effectiveness of e-mails as delivering method of the behavioral intervention. Second, we will evaluate the validity of social norms feedback as a procedure for changing physicians prescriptive practice in the Latin American context. Third, given concerns about possible deterrence effects of communications with strong language or implying potential punitive actions from regulatory agencies, our intervention separates social norm and potential deterrence effects avoiding the use of coercive wording and obviating any mention to potential punishments from authorities. Fourth, we are also interested in knowing more about the acceptability of the intervention from the participants' point of view. For this purpose, a brief post-intervention survey will be implemented. We hypothesize that the treated group will reduce their rates of nimodipine prescriptions in comparison with the control group. We also expect that the intervention will be cost-effective and well accepted by the participants.

139 **Trial design {8}**

140 Pragmatic parallel group randomized controlled trial with two arms (1:1 allocation ratio).

141

142

143 **Methods: Participants, interventions and outcomes**

144 **Study setting {9}**

145 The study will be entirely carried at the National Institute of Social Services for Retired and  
146 Pensioners (in Spanish, Instituto Nacional de Servicios Sociales para Jubilados y Pensionados,  
147 INSSJP). The INSSJP was created in 1971 with the objective of providing universal coverage of  
148 social and health services to the specific needs of the retired and pensioners of Argentina. The  
149 INSSJP is the largest health insurance agency in Argentina and South America, with 5.089.021  
150 affiliates in 2015. Approximately, 65% of the Argentinean citizens older than 60 years old are  
151 affiliates of the INSSJP.

152

153 **Eligibility criteria {10}**

154 The initial study population will be the general practitioners of the INSSJP-PAMI system who  
155 prescribed at least one package of nimodipine during the last quarter of 2018 (n = 8965). The  

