156 sample under study will be the high prescribers within that population, defined as the top 25%  
157 prescribers of nimodipine during the last quarter of 2018.

158

159 **Who will take informed consent? {26a}**

160 As in previous similar studies (Hallsworth et al., 2015; Sacarny et al., 2018) the present trial will  
161 not require informed consent from prescribers, since obtaining consent would invalidate the results.  
162 The study did not involve contact or direct intervention on patients, nor access to their personal  
163 information.

164

165 **Additional consent provisions for collection and use of participant data and biological  
166 specimens {26b}**

167 Not applicable

168

169

170

171 **Interventions**

172 **Explanation for the choice of comparators {6b}**

173 The control condition is conceived as a non-specific placebo comparator that replicates the format  
174 of the treatment intervention without its active ingredients (evidence-based information about  
175 nimodipine plus peer comparison). The comparator is supposed to control for non-specific  
176 behavioral factors such as receiving attention or raising awareness about over-prescription as a  
177 general problem in medical practice. Also, the placebo e-mails will allow to check if both groups  
178 open the e-mails at similar rates.

179

180 **Intervention description {11a}**

181 During the intervention phase of the study, participants in the two arms of the trial will receive two  
182 e-mail communications. The messages will be framed as a communicational campaign for  
183 improving the quality of pharmacological practice. In the case of the treatment arm, the first  
184 communication will include two components: a) evidence-based information about the adequate use  
185 of nimodipine and b) the participant's level of prescription of nimodipine compared to their peers.  
186 The second message, 3 months later, will include information on nimodipine prescriptions' change  
187 observed by the participant during the previous quarter ("change" or "no change"). The e-mail  
188 directed to those that reached a relative reduction of 10% of prescriptions compared to their  
189 baseline average will include an acknowledgement of their success intended to work as a verbal  
190 reinforcement of the positive behavior ("acknowledgement version"). The e-mail to the rest of  
191 participants will intend to potentiate the social norm component by stating that many of their  

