**Outcomes {12}**

The primary outcome will be the cumulative total number of nimodipine prescriptions per 1000 prescriptions of all drugs made by the targeted practitioners during the 6 months after the intervention started.

As secondary outcome, we will estimate the annual monetary savings attributable to our intervention at the national level (for details see Statistical Methods section). Also, we will perform a sub-sample analysis of the physicians that open the e-mails, as informed by the mailer system. Finally, we will assess the acceptability of the intervention through a brief *ad hoc* survey to the intervention arm participants at the end of the study (six months after the start of the intervention).

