**Participant timeline {13}**

The number of nimodipine prescriptions for each physician is registered monthly during a year prior to the first e-mail (baseline period) and during the semester after (intervention period).

Follow-up period will eventually comprise a year after the intervention period ends.

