**Assignment of interventions: allocation**

**Sequence generation {16a}**

Selected prescribers will be randomly allocated to control and treatment (1:1 ratio) controlling for number of nimodipine prescriptions over the last trimester of 2018. Randomization is performed with R software with the package RandomizeR.

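### Allocation is controlled for a one-quarter nimodipine count while the primary outcome is a rate per 1000 prescriptions, so the outcome's own baseline is only partly balanced

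*Protocol*

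**What the plan says.** - **Entry.** Eligibility criteria {10} starts from GPs who "prescribed at least one package of nimodipine during the last quarter of 2018 (n = 8965").
- **Outlier cut.** In Recruitment {15}, "the outlier threshold was set at the 97,5th percentile of nimodipine box prescriptions over the last trimester of 2018".
- **Enrichment.** The same section then says that "once outliers were removed, the top 25% prescribers of nimodipine were selected". No metric is named for this ranking.
- **Allocation.** Sequence generation {16a} randomises 1:1, "controlling for number of nimodipine prescriptions over the last trimester of 2018". How this control is carried out (strata, blocks or otherwise) is not described.
- **Outcome.** Outcomes {12} defines the primary outcome as the "cumulative total number of nimodipine prescriptions per 1000 prescriptions of all drugs made by the targeted practitioners" over six months.
- **Baseline data.** Under Participant timeline {13}, each GP's nimodipine prescriptions are "registered monthly during a year prior to the first e-mail (baseline period").
- **Analysis.** Statistical methods {20a} plans a mixed-effects repeated-measures ANOVA, and a multiple linear regression that adjusts for baseline prescription levels. It does not say whether those levels are a count or a rate.

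Total prescribing volume is not mentioned in selection or allocation, and no reason is given for the change of scale.

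**The concern.** Controlling allocation for a baseline variable helps to the extent that the variable predicts the outcome. The best candidate is usually the baseline value of the outcome itself, here nimodipine per 1000 prescriptions before the first e-mail. The protocol uses the numerator alone, from a single quarter. Two GPs with the same count can have very different rates if one writes several times as many prescriptions as the other. Arms matched on the count can therefore still differ by chance in baseline rate.

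At stake are baseline comparability on the analysed scale and some precision. Both matter more when the target effect is very small, and the protocol states d = 0.05. The analysis would recover much of the loss if it adjusted for the baseline rate, but the scale of the adjustment variable is left open.

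**Working it through.** **Inputs from the protocol.** 8965 GPs at entry; outlier cut at the 97.5th percentile; top 25% kept; 1:1 allocation; stated effect d = 0.05 and minimum N = 1030 (Sample size {14}). The protocol gives no distribution of prescribing volume or of nimodipine rate.

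**The plan's own figure.** N = 1030 can be neither confirmed nor refuted, because the number of measurements and their correlation are not stated. It arises, for example, for a within-between test with f = 0.05, 3 measurements and correlation 0.2, or with f = 0.025, 3 measurements and correlation 0.8. The present point does not depend on it.

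**Step 1: GPs per arm.** 8965 x 0.975 = 8741; x 0.25 = 2185; / 2 = about 1092 per arm, before the checks on provider status and active e-mail address.

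**Step 2: chance imbalance in baseline rate, no balancing.** The standard error of a standardised mean difference between two arms of n is sqrt(2/n). With n = 1092 this is sqrt(2/1092) = 0.043 SD. If only the stated minimum of 1030 were randomised (515 per arm), it would be sqrt(2/515) = 0.062 SD.

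**Step 3: what balancing on the count removes.** If the count were perfectly balanced and had correlation r with the baseline rate among selected GPs, the remaining standard error would be sqrt(2/n) x sqrt(1 - r²). The documents do not give r, so it was simulated under these assumptions:
- quarterly volume lognormal, median 1500 prescriptions, log-SD 0.3 to 1.0;
- nimodipine rate lognormal, median 4 per 1000, log-SD 0.5 to 1.0;
- volume independent of rate, and Poisson counts;
- the protocol's steps applied in order: at least one box, drop above the 97.5th percentile of counts, keep the top 25% by count.

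| Case | Volume log-SD | Rate log-SD | r | Remaining SE (1092 per arm) |
|---|---|---|---|---|
| Count tracks rate best | 0.3 | 1.0 | 0.75 | 0.0428 x sqrt(1 - 0.5625) = 0.028 SD |
| Count tracks rate worst | 1.0 | 0.5 | 0.12 | 0.0428 x sqrt(1 - 0.0144) = 0.042 (0.0425) SD |

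The more volume varies relative to the rate, the less the count protects. At the lower end of r, count balancing does almost nothing for the baseline rate. These are best-case figures for count balancing, since they take the balance as perfect. Here r relates the Q4 count to the rate in that same quarter.

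**Step 4: against the target.** 0.028 to 0.043 SD is 57% to 86% of d = 0.05 (0.0283 / 0.05 and 0.0428 / 0.05). If the 0.05 was entered as Cohen's f, then for two equal groups d = 2f = 0.10, and the shares halve to 28% and 43%. In an unadjusted comparison the imbalance passes to the outcome multiplied by the correlation between baseline and follow-up rate, so these shares are upper limits.

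**The case against.** The strongest reply is that randomisation already deals with this. Chance imbalance is part of the ordinary standard error and is not added to it. It does not bias the comparison, and chance high quarters in Q4 2018 regress equally in both arms. That stands. It is also true that 0.043 SD is small in absolute terms, and that the planned regression, or a repeated-measures model with baseline months on the outcome scale, could remove most of it. That stands only if the baseline is the rate, which Statistical methods {20a} does not say.

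A reader might infer something stronger: that the sample consists partly of high-volume GPs rather than high-rate prescribers, so the top 25% should be drawn again by rate. The documents do not support that.
- The metric for the top-25% step is not labelled. A count is the natural reading beside a box-based cut, but it is an inference.
- The share of selected GPs with ordinary rates cannot be computed from the documents. Under the assumptions above, 16% to 59% fall outside the top quartile by rate, a range too wide to act on.
- Ranking by count has a rationale. The protocol's background gives nimodipine a single, usually inpatient, indication, so outpatient boxes are largely the target. The savings objective also concerns items prescribed.
- Rate ranking does not clearly gain power. Take a 10% relative effect, log-SDs of 0.6 (volume) and 0.7 (rate), median volume 1200 and median rate 6 per 1000. With adjustment for the baseline rate, the standardised effect is 0.465 under count selection and 0.443 under rate selection. Without adjustment it is 0.173 against 0.309. What matters is the baseline in the model rather than who is enrolled.

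A reader might also infer that the peer message would be untrue or lose credibility for some recipients. The e-mail's metric is not given, and a statement about boxes would be true.

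**Conclusion.** The point holds in limited form. Allocation is controlled for a one-quarter count and the primary outcome is a rate, so the arms are only partly balanced on the outcome's baseline. The standard error of that imbalance is 0.043 SD without balancing, which follows from the protocol's own figures. With perfect count balance it is 0.028 to 0.043 SD, which rests on assumed lognormal volumes and rates, independent of each other. Either is a material fraction of the effect the trial says it targets. The consequence is some lost precision and weaker baseline comparability, without bias or an inflated error rate. The loss would be largely recovered in analysis if the adjustment baseline were the rate, so the open wording in Statistical methods {20a} is the second half of the same point. No change to the selected sample follows from this.

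**What to change.** 1. In Sequence generation {16a}, control the randomisation for each GP's nimodipine prescriptions per 1000 prescriptions of all drugs over the 12 months before the first e-mail, instead of or together with the Q4 2018 count. State how the control is done.
2. In Statistical methods {20a}, define the baseline prescription levels in the regression as that same 12-month rate.
3. In Recruitment {15}, name the metric used to rank the top 25%. If it is the count, one sentence of justification is enough.

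The cost is small. Participant timeline {13} mentions only nimodipine numbers for the baseline year, so the all-drug totals for those months must also be drawn. The protocol takes all data from one prescriptions database, and the outcome needs the same denominator after the intervention. The allocation must be re-run before the first e-mail. The number of GPs does not change. If allocation has already been made, item 2 alone recovers most of the benefit.

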**Assignment of interventions: allocation**

**Sequence generation {16a}**

Selected prescribers will be randomly allocated to control and treatment (1:1 ratio) controlling for number of nimodipine prescriptions over the last trimester of 2018. Randomization is performed with R software with the package RandomizeR.

**Concealment mechanism {16b}**

Not applicable

**Implementation {16c}**

A study investigator (AT) analysed the 2018 database of prescription of nimodipine for selecting those who met inclusion criteria. Before the intervention begins, she will randomly assign the selected participants to treatment or control groups. AT will not participate in the implementation of the interventions nor in the statistical analysis of the results.

268 **Assignment of interventions: Blinding**

269 **Who will be blinded {17a}**

270 Participants in treatment group will likely be aware of the interventions they were assigned to but  
271 unaware that they were involved in a trial. Physicians names and other identificatory information is  
272 accessible only to the principal investigator (FT) for matching successive monthly waves of  
273 prescription rates, but this information will be blind to any other team group and INSSJP-PAMI  
274 authorities.

275

276 **Procedure for unblinding if needed {17b}**

277 Not needed.

278

279 **Data collection and management**

280 **Plans for assessment and collection of outcomes {18a}**

281 All data is obtained from the prescriptions database of the INSSJP-PAMI.

282

283 **Plans to promote participant retention and complete follow-up {18b}**

284 Since the intervention does not involve any evaluation interview or the completion of  
285 questionnaires by the participants, there is no mechanism in place to ensure retention. All the  
286 necessary data is obtained from the INSSJP-PAMI prescription system that automatically records  
287 the prescribing behavior of physicians.

288

289 **Data management {19}**

290 All data is obtained from the prescriptions database of the INSSJP-PAMI.

291

292 **Confidentiality {27}**

293 Personal information needed to track the prescriptive behavior of physicians during the trial period  
294 is managed only by the principal investigator (FT) and converted to a numerical ID for all the  
295 remaining analysis.

296

**Plans for collection, laboratory evaluation and storage of biological specimens for genetic or molecular analysis in this trial/future use {33}**

Not applicable.

**Statistical methods**

**Statistical methods for primary and secondary outcomes {20a}**

The primary outcome will be analyzed using a mixed effects repeated measures ANOVA model. Comparisons between groups will be made using one-way ANOVA, while a multiple linear regression analysis will be implemented to evaluate the predictive value of the group condition controlling for baseline prescription levels. Finally, the Pearson chi-square test will be employed to analyze categorical variables.

To estimate the annual monetary savings attributable to our intervention at the national level, we will make the following calculations: first, we will estimate the number of items that would have been prescribed in the absence of the treatment. This number corresponds to the multiplication of the treatment effect times the number of items prescribed by an average physician in the control group during one year. We then multiply this quantity by the direct average price of each item (in U\$S), according to the registers of the INSSJP-PAMI. This gives an estimated benefit per-physician/year. Should this intervention be implemented for all eligible physicians in the country during a year, *the total estimated benefit* is projected as the product between the benefit per-physician/year and the total number of doctors included in the study in both groups. As opposed to other similar interventions (such as Hallsworth et al., 2016) we will not incur in any substantial per-physician cost, as we will implement our treatment via e-mail instead of post mail. The main cost would thus be related to the analysis of the data to retrieve the top 25% of high-prescribers and the design of the letter. Being conservative, we budget as *total estimated cost* two full-time weeks of work (as we sent two communications) of a public servant for these tasks according to national statistics. Finally, the total estimated cost-benefit of the intervention is the *total estimated benefit* minus the *total estimated cost*.

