**Sample size {14}**

To calculate our minimum sample size, we used GPower 3.1. Power calculation estimated a sample size of 1030 participants for detecting an effect size of  $d=0.05$ , with 80% of statistical power and a significance level of 0.05 in the repeated measures ANOVA.

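### The primary outcome is one six-month rate per GP, but it is assigned to a repeated measures ANOVA with no fixed time factor or contrast, alongside two unranked group comparisons

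*Protocol*

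**What the plan says.** Protocol, Outcomes {12}: "The primary outcome will be the cumulative total number of nimodipine prescriptions per 1000 prescriptions of all drugs made by the targeted practitioners", counted "during the 6 months after the intervention started". With GPs as the randomised units, this is one number per GP.

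Protocol, Statistical methods {20a}: "The primary outcome will be analyzed using a mixed effects repeated measures ANOVA model". The next sentence adds: "Comparisons between groups will be made using one-way ANOVA, while a multiple linear regression analysis will be implemented", the regression being there to "evaluate the predictive value of the group condition controlling for baseline prescription levels". The section gives no time levels and no tested term for the first model. It names no outcome or rank for the other two. It then uses a treatment effect in the national savings calculation without saying which analysis supplies it.

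Protocol, Participant timeline {13}, says that prescriptions are recorded monthly for a year before the first e-mail and for six months after it. Sample size {14} says "Power calculation estimated a sample size of 1030 participants" for d=0.05, 80% power and a 0.05 level in the repeated measures ANOVA. Sequence generation {16a} controls allocation for the nimodipine count in the last quarter of 2018.

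**The concern.** The named model cannot be fitted to the named outcome. To run it, the analyst must replace the six-month rate with monthly or pre/post values, and then choose which term carries the trial's claim. Those choices lead to different estimates and different error rates, and the protocol leaves them open.

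Two further analyses of the group difference sit beside it. One ignores baseline. The other adjusts for it and answers the stated question most directly, but is described only in terms of predictive value. If the analyses disagree, the text permits the claim to rest on whichever is quoted. The same ambiguity passes into the savings estimate, since a multi-degree-of-freedom group-by-month test gives no single effect to multiply.

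**Working it through.** **1. The plan's own figure.** Could 1030 show which term is meant? As a plain two-mean comparison with d=0.05, n per arm = 2(1.96+0.8416)²/0.05² ≈ 6280, or 12560 in total; 515 per arm gives 12% power. So 1030 must come from repeated-measures settings that are not stated. Noncentral-F calculations for two groups give:
- interaction, 3 measurements, f=0.05, correlation 0.2: N=1030
- interaction, 3 measurements, f=0.025 (d=0.05 converted), correlation 0.8: N=1030
- between-group term, 4 measurements, f=0.05, correlation 0.1: N=1024

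The figure is therefore not uniquely reproducible, and it does not reveal the tested term.

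**2. Dilution under one reading.** Suppose the group main effect is taken over all 18 recorded months and the true effect δ exists only in the last 6. The model then estimates (12×0 + 6×δ)/18 = δ/3.

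**3. Simulation of the possible readings.** Settings: 515 GPs per arm, 12 pre and 6 post months, unit monthly SD, 1000 runs per scenario, effect 0 or 0.15 SD. Four assumed covariance structures were used: GP intercept share 0.3 to 0.5, with AR(1) month correlation 0, 0.5 or 0.8. Monte Carlo error is about 0.7 points near 5%.

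| Reading | Type I error | Power at 0.15 SD |
|---|---|---|
| Group main effect, 18 months | 4–6% | 17–24% (mean estimate about 0.05) |
| Random-intercept group-by-period on months | 6% at AR 0; 22–35% at AR 0.5–0.8 | not comparable when inflated |
| Uncorrected group-by-month, 18 months | 5% at AR 0; 9–14% at AR 0.5–0.8 | not comparable when inflated |
| Uncorrected group-by-month, 6 post months | 4% at AR 0; 7–9% at AR 0.5–0.8 | 5–8%: a constant effect gives no interaction |
| Pre/post group-by-time (change score) | 5–6% | 89–100% |
| One-way ANOVA on six-month mean | 4–6% | 75–88% |
| Baseline-adjusted regression | 5–6% | 92–100% |

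A group main effect over the six post months alone is the same test as the one-way ANOVA row. Quoting the best of change score, one-way ANOVA and adjusted regression gave 9–11% type I error. For three independent tests the figure would be 1 − 0.95³ = 14.3%.

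**4. Cost of the favourable reading.** An upper bound on the eligible number follows from Eligibility criteria {10} and Recruitment {15}: 8965 × 0.975 × 0.25 ≈ 2185, before removing GPs who have left or have no active e-mail. Assume equal pre and post variances and baseline-to-outcome correlation r. Then z = δ√(N/4)/k and power ≈ Φ(z − 1.96), where k = 1 for one-way ANOVA, √(2(1−r)) for change and √(1−r²) for adjusted regression. With δ = 0.12 SD of the six-month mean, δ√(N/4) = 0.12 × 23.37 = 2.805.
- One-way ANOVA: z = 2.805, power 80%.
- Change, r=0.67: k = 0.812, z = 3.45, power 93%.
- Adjusted, r=0.67: k = 0.742, z = 3.78, power 97%.
- r=0.95: both change and adjusted about 100%.

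At δ = 0.05 SD, change gives about 30% (r=0.67) to 96% (r=0.95); adjusted gives 35% to 96%.

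**The case against.** The strongest reply has three parts.

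First, the harmful readings are not in the plan. The protocol does not say that 18 months enter the model, that the main effect is tested, or that the covariance is random-intercept only. The hypothesis in Objectives {7}, a reduction in the treated group relative to control, points most naturally to a group-by-time term. In its two-level pre/post form, that term keeps the full effect and the nominal error rate. This stands.

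Second, only the repeated measures ANOVA is tied to the primary outcome, and Sample size {14} attaches the 0.05 level to it alone. The section heading covers secondary outcomes too, so the other two analyses need not compete with it. This also stands: the first model has nominal precedence.

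Third, time levels, covariance and sphericity corrections are usually left to a statistical analysis plan, which is not at hand. That is right, and their absence is not the point made here. What remains is a mismatch inside the protocol: it defines one quantity as primary and assigns it to a model that needs different data, with further group comparisons left unlabelled.

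**Conclusion.** The outcome definition and its named analysis do not fit together, and the protocol does not say which contrast decides the trial.

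The size of the consequence depends on the reading. It runs from a threefold dilution (18-month main effect), through type I error of 7–35% (month-level tests under AR 0.5–0.8), to a modest loss of precision (93% against 97% power at r=0.67, 0.12 SD, N=2185). The effect sizes, correlations and covariance structures are assumptions, and 2185 is an upper bound.

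A reader might infer that the planned model necessarily dilutes the effect or understates its error. The documents do not support that, because they never choose the settings that cause it, and a pre/post contrast has neither fault. A reader might also infer that three tests at 0.05 compete as equals. The text permits selective quotation, with 9–11% type I error if the best of three is taken, but it does not plan it.

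**What to change.** Name one primary analysis that matches Outcomes {12}: linear regression of each GP's six-month rate on arm, the same rate over the baseline year and the last-quarter-2018 nimodipine count used in allocation, with heteroscedasticity-robust standard errors. Report the arm coefficient with its 95% CI, and state that this coefficient is the treatment effect used in the savings calculation. Label the repeated measures model as a supportive description of the time course, and the one-way ANOVA as a supportive unadjusted comparison.

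The cost is wording. The baseline-adjusted regression is already planned and all the variables are already recorded. The sentence in Sample size {14} should then name the same model and state the baseline-to-outcome correlation it assumes.

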## Introduction

### Background and rationale {6a}

The prescription of drugs without evidence is a significant public health problem. In the case of people over 65 years, polypharmacy and adverse effects could have negative consequences for health and quality of life. Also, undue prescriptions cause burdensome costs to the health system without any benefit for the patient. Among the medications improperly prescribed in the population of older adults, there is a diverse set of drugs used for the treatment of patients with mild cognitive impairment and dementias, including antioxidants, nootropic agents, vitamins, biological products and vasodilators (Rojas et al., 2010; Rojas et al., 2013). Currently 46.8 million people live with dementia across the world, and this number is expected to double every 20 years, reaching an estimated number of people living with dementia as high as 131.5 million by 2050 (Prince et al., 2015). The only worldwide recommended pharmacological treatment for different dementias are the acetylcholinesterase enzyme inhibitors (donepezil, galantamine and rivastigmine), and the NMDA receptor antagonist memantine (NICE, 2018; McKeith et al., 2017; Schmidt et al., 2015). In the case of Mild Cognitive Impairment, a pre-dementia syndrome, there is no recommended drug for its treatment (Petersen et al., 2018).

Previous reports in Argentina revealed that the prescription of recommended drugs for the treatment of cognitive impairment accounted for between 54 and 59% of total indications, meanwhile non-recommended drugs represented between 41 and 45 %. Among these, the most used drug was nimodipine (Rojas et al., 2010, 2013). According to the current evidence, nimodipine has a single indication for the treatment of acute subarachnoid hemorrhage, which is usually administered for short periods during the hospitalization period. There is not enough evidence for the use of nimodipine in the prevention or treatment of cognitive impairment on an outpatient and prolonged basis.

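### The savings formula equals the drug-spend saving only if no priced drug replaces nimodipine, and the protocol neither states nor checks that condition

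*Protocol*

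**What the plan says.** Outcomes {12} names the quantity of interest: "we will estimate the annual monetary savings attributable to our intervention at the national level". Statistical methods {20a} then writes the calculation out in full:

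- The number of avoided items per physician is "the multiplication of the treatment effect times the number of items prescribed by an average physician in the control group during one year".
- Each is valued at its full price: "We then multiply this quantity by the direct average price of each item". The protocol continues: "This gives an estimated benefit per-physician/year".
- The total benefit is "the product between the benefit per-physician/year and the total number of doctors included in the study in both groups".
- The total cost is "two full-time weeks of work" by a public servant, and the final cost-benefit figure is benefit minus that cost.

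Staff time is the only deduction. No step subtracts spending on drugs prescribed instead of nimodipine, and no other section plans to measure such prescribing.

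Background and rationale {6a} says of the same therapeutic area that "there is a diverse set of drugs used for the treatment of patients with mild cognitive impairment and dementias". Vasodilators, vitamins and nootropics are among its examples of improperly prescribed drugs. It also names the recommended agents (the cholinesterase inhibitors and memantine). It puts non-recommended drugs at 41 to 45% of indications, with nimodipine the most used among them.

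**The concern.** A saving attributable to an intervention is the difference in spending between what happens with it and what would have happened without it. The formula measures one component of that difference, the nimodipine items no longer prescribed. A physician who stops nimodipine still has the same patient, and the Background shows that other drugs are in use for that patient. The treatment e-mails described in {11a} carry evidence and peer feedback on nimodipine; nothing in that description addresses substitutes.

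If some avoided items are replaced by another priced drug, the payer saves less than the formula reports. Cost is part of the trial's policy message: the Abstract presents the method as a way to cut unnecessary costs, and Objectives {7} expects cost-effectiveness. A payer deciding whether to scale up would rely on a figure that assumes no replacement without saying so.

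**Working it through.** **Plan's own figure.** There is none to reproduce. The protocol gives no treatment effect in items, item count, price or savings total, so the check is algebraic.

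**Inputs from {20a}** (items are read as nimodipine items)

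- Q = avoided items per physician per year (treatment effect x items per average control physician)
- P = direct average price per item
- N = doctors in both arms
- C = cost of two staff weeks

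**Inputs not in the document (assumed, with a range)**

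- s = share of avoided items replaced by another drug, 0 to 1
- p = replacement price divided by nimodipine price, 0.25 to 2

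**Step 1, the formula as written.** Stated benefit = N x Q x P. Stated cost-benefit = N x Q x P - C.

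**Step 2, with replacement.** Each replaced item costs p x P, so

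benefit = N x Q x (P - s x p x P) = N x Q x P x (1 - s x p).

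The ratio of true to stated benefit is 1 - s x p. C is the same in both versions, so the ratio applies to the benefit before staff cost is deducted.

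**Step 3, numbers.** True benefit as a share of the stated benefit:

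| s | p = 0.25 | p = 0.5 | p = 1 | p = 2 |
|---|---|---|---|---|
| 0 | 1.00 | 1.00 | 1.00 | 1.00 |
| 0.10 | 0.975 | 0.95 | 0.90 | 0.80 |
| 0.25 | 0.94 | 0.875 | 0.75 | 0.50 |
| 0.50 | 0.875 | 0.75 | 0.50 | 0.00 |
| 1.00 | 0.75 | 0.50 | 0.00 | -1.00 |

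Seen from the other side, the stated figure exceeds the true one by 1/(1 - s x p) - 1. At p = 1 this is 11% for s = 0.10, 33% for s = 0.25 and 100% for s = 0.50. The two agree only when s x p = 0, and the saving disappears once s x p reaches 1.

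**Step 4, would another planned analysis reveal switching?** The primary rate cannot. Take, purely as illustration, 100 nimodipine items in 1000 prescriptions, of which 20 are avoided. If all 20 are replaced, the rate is 80/1000 = 80.0 per 1000. If all 20 are simply stopped, it is 80/980 = 81.6 per 1000. The two cases are nearly indistinguishable on this scale, yet at p = 1 the drug-spend saving is nil in the first and full in the second.

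**The case against.** The strongest reply is that the harm is hypothetical. The Background shows that other drugs exist, not that physicians who drop nimodipine turn to them. It also says that mild cognitive impairment has no recommended drug, so stopping without replacement is a plausible result. Every entry in the table below 1.00 comes from assumed inputs. This stands: the size is unknown and may be zero.

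A reader might infer three stronger points, none of which the protocol supports:

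- *That the saving is overstated.* It can be, but nothing in the document establishes that switching occurs. The formula also leaves out possible gains, since the Background links undue prescribing to adverse effects and polypharmacy.
- *That a gross figure is passed off as net.* The protocol never uses that term, states that it uses a direct item price, and does deduct staff time. The omission concerns replacement drugs only. The wording in Outcomes {12} is nevertheless broader than avoided nimodipine spending.
- *That the primary outcome is defective.* The main aim is to reduce nimodipine prescribing, and a nimodipine rate answers that aim whether or not another drug takes its place.

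There are also practical objections to a remedy. The protocol does not say that the extract records indication, and {26a} rules out access to patients' personal information. A basket of vitamins or vasodilators could therefore include prescribing for other conditions. Prices for drugs other than nimodipine are not mentioned. A switch to a drug the Background classes as recommended should not be read simply as wasted money. These objections shape the fix but do not remove the need for it.

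**Conclusion.** The point holds for the secondary savings outcome. The protocol itself fixes a formula that equals the attributable drug-spend saving only under zero priced replacement, and that condition is neither stated nor checked. The size cannot be determined from the document. Under assumed values, the true benefit is 100% of the stated one at s = 0, 75% at s = 0.25 with p = 1, and 50% at s = 0.5 with p = 1. The less favourable corners of the table are arithmetically possible but have no more support than the favourable ones. The conclusion is limited to drug spending; it does not claim a full economic net benefit in either direction.

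**What to change.** 1. Label the result of the {20a} formula as avoided nimodipine spending before replacement prescribing, and use that label wherever the savings outcome is named.
2. Add a baseline-adjusted comparison between the randomised arms of drug cost per physician from the INSSJP-PAMI database, with a confidence interval. Use a set of named substitute drugs for cognitive impairment, listed before the data are seen, together with nimodipine. Show recommended and non-recommended drugs separately, because a switch to a recommended drug is not undue cost.
3. Report total drug cost per physician as a sensitivity analysis. It needs no choice of basket.
4. If prices for the other drugs cannot be obtained, compare prescription counts of the listed drugs between arms instead. That still shows whether switching took place.

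**Cost.** A further data extract is needed. The primary denominator already requires counts of all drugs from this database, but baseline data on the substitutes would have to be drawn too, since Participant timeline {13} mentions only nimodipine. The interval will be wider, the basket will contain some prescribing for other indications, and the saving may prove less favourable. The primary outcome and its analysis do not change.
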